**Methods/Design:**

This two-arm cluster randomized controlled trial (with integral economic evaluation and qualitative study) is set in general practices in three UK Primary Care Trusts. Practices are randomized to one of two groups with patients referred to either an ICCD (intervention) or to hospital care (control).

**Intervention group:** GP practices in the intervention arm have the opportunity to refer patients to an ICCD - a multidisciplinary team led by a specialist nurse and a diabetologist. Patients are reviewed and managed in the ICCD for a short period with a goal of improving diabetes and cardiovascular risk factor control and are then referred back to practice.

or

**Control group:** Standard GP care, with referral to secondary care as required, but no access to ICCD.

Participants are adults aged 18 years or older who have type 2 diabetes that is difficult for their GPs to control. The primary outcome is the proportion of participants reaching three risk factor targets: HbA_1c_ (≤7.0%); blood pressure (<140/80); and cholesterol (<4 mmol/l), at the end of the 18-month intervention period. The main secondary outcomes are the proportion of participants reaching individual risk factor targets and the overall 10-year risks for coronary heart disease(CHD) and stroke assessed by the United Kingdom Prospective Diabetes Study (UKPDS) risk engine. Other secondary outcomes include body mass index and waist circumference, use of medication, reported smoking, emotional adjustment, patient satisfaction and views on continuity, costs and health related quality of life. We aimed to randomize 50 practices and recruit 2,555 patients.

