#### Practice randomization

Practices recruited to the study were randomized to an intervention or control arm, stratified by practice size and PCT to achieve similar numbers in each arm of the trial. Practices in the intervention arm have access to ICCD service. The study design anticipated that up to 30% of patients in any practice might be eligible for referral to ICCD. Those practices randomized to usual care are issued with local guidelines and continue to manage their patients (including hospital referrals) in the usual way.

Randomization, stratified by area and GP practice size, was undertaken independently of the trial team by Warwick Clinical Trials Unit.

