### Analysis

#### Statistical analysis

Intention-to-treat (ITT) comparisons of the two groups will be conducted, with the primary dependent variable being the proportion of patients achieving all three clinical targets at 18 months. The main analysis will be based on all patients recruited to the study. As some drop-outs and losses are inevitable, sensitivity style analyses are planned. Missing data imputation will use ‘last observation carried forward’ (LOCF). Secondary analyses will exclude all observations with missing values. Analyses will use a mixed effects logistic regression model, and will adjust for baseline characteristics at both practice and individual level. The former may include practice size and deprivation index, and the latter age, gender, BMI, ethnicity, employment status, educational level and length of time since diagnosis. Characteristics will be included using a forward selection model-building strategy, with only variables significant at the 10% level selected. Odds ratios (OR) will be estimated with 95% confidence intervals, adjusting for potential confounding variables and allowing for the effect of the cluster randomization [43].

Further analysis will examine secondary outcomes (achievement of individual targets for blood pressure, HbA1c and lipids), again adjusting for confounders and allowing for the cluster randomization. In addition, UKPDS 10-year risk scores for CHD and stroke will be analyzed using a linear mixed model.

Tertiary analysis of questionnaire responses will consider longitudinal continuity, flexible continuity, relational continuity and term and boundary continuity following the NCCSDO methodology on ‘continuity of care in type 2 diabetes’ [44]. We will also compare the levels of ICCD use by the intervention practices, and the drop-out rates for all practices.

Finally, all analyses will be re-run with added data from MIQUEST covering all diabetes patients in a practice whether recruited to the trial or not [45]. This will lessen the number of variables available, but otherwise all analyses for primary and secondary endpoints will be repeated.

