## Discussion

The present study will provide a robust estimate of the effects of introduction of intermediate care clinics for diabetes to support the care of patients in UK primary care, and the costs associated with any improvements in outcomes produced. The ICCD model aims to deliver high quality care through a multidisciplinary, locality-based team, with the added opportunity for developing professional expertise in the community. The results of this trial will be of direct policy relevance to the development of diabetes services in the UK, and will provide clinical commissioning groups with evidence to inform decisions on commissioning services to improve control in T2DM. Diabetes and service reconfiguration are both national research priorities but there is an urgent need to base policy on evidence. Modeling suggests the ICCDs will be cost-effective in reducing complications and consequent hospital admissions, as well as producing societal benefits such as reduced incapacity to work. If results from this short-term evaluation are positive they will provide an initial evidence base for adoption and for longer-term evaluations to assess the benefits predicted from modeling. The qualitative study will help identify factors influencing service uptake and, if the trial finds no significant effect, why efficacy was not demonstrated. Forty-nine practices have been randomized and 1,997 patients recruited to the trial. Follow up finished in October 2011 and the results will be available in late 2012. It is not possible at present to comment on the effectiveness or cost-effectiveness of an ICCD service.

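### The primary model's covariates are chosen by forward selection on the outcome data, and nothing keeps the randomization stratifiers (practice size and PCT) in it

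*Protocol article*

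**What the plan says.** The article's Practice randomization section states that practices were randomized "stratified by practice size and PCT to achieve similar numbers in each arm of the trial". The same section repeats this as "Randomization, stratified by area and GP practice size, was undertaken independently of the trial team". I take area to mean PCT; there are three of them.

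The Statistical analysis section sets the model: "Analyses will use a mixed effects logistic regression model, and will adjust for baseline characteristics at both practice and individual level". For practice-level covariates it says "The former may include practice size and deprivation index", and for individual-level ones "the latter age, gender, BMI, ethnicity, employment status, educational level and length of time since diagnosis". The rule for entry is: "Characteristics will be included using a forward selection model-building strategy, with only variables significant at the 10% level selected". No primary model with a fixed covariate set is described, and no variable is exempted from the screen. The same section says secondary outcomes will again be adjusted for confounders.

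**The concern.** Three things do not fit together.

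- **The model does not follow the randomization.** Stratifying balances the arms on PCT and practice size. The treatment estimate then varies less than it would under simple randomization. A model that omits a prognostic stratifier leaves its variation in the error term and reports a standard error that is too large.
- **The estimand moves with the data.** The odds ratio from a logistic model is non-collapsible: its value depends on which covariates are in the model, even without confounding. If the outcome data choose the covariates, they also choose which conditional odds ratio is reported, and the interval takes no account of that choice.
- **The section can contradict itself.** It promises adjustment at both practice and patient level, yet the screen could leave no practice-level covariate at all.

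At stake are the precision and the prespecification of the trial's headline result.

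**Working it through.** **Inputs.** Practices and patients: "Forty-nine practices have been randomized and 1,997 patients recruited to the trial" (Discussion). ICC 0.05 for the combined outcome (Sample size section). Entry threshold 10% and the covariate lists (Statistical analysis section). The share of between-practice variance due to any covariate is not in the article, so it is an assumption shown as a range.

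**Check on the ICC.** The plan gives no figure on covariate selection itself. Its total of 2,848 for 20% versus 30% does reproduce with ICC 0.05. The continuity-corrected size is 313 per arm and the design effect is 1 + 71 × 0.05 = 4.55. Then 313 × 4.55 ≈ 1,424 per arm, or 2,848 in all. Covariate choice does not enter that calculation.

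**How open the model is.** Nine candidates are named (2 practice-level, 7 patient-level), giving 2^9 = 512 possible covariate sets. If none were prognostic and the tests were independent, the chance that at least one enters is 1 − 0.9^9 = 61%.

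**Chance that a useful practice-level covariate survives.**
- Mean practice size: 1,997/49 = 40.8.
- Reliability of a practice mean: 40.8 × 0.05 / (1 + 39.8 × 0.05) = 0.68.
- R² at practice level = share × 0.68; non-centrality = 49 × R²/(1 − R²); power from the non-central F(1, 47) at 10%.
- CI widening if the covariate is omitted = 1/√(1 − R²) − 1.

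| Assumed share of between-practice variance | R² | Non-centrality | Kept | CI widening if omitted |
|---|---|---|---|---|
| 5% | 0.034 | 1.73 | 37% | 1.8% |
| 10% | 0.068 | 3.59 | 59% | 3.6% |
| 20% | 0.136 | 7.74 | 86% | 7.6% |

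The "kept" column applies to practice size or deprivation. For PCT, which is not a named candidate, the last column applies whenever it is left out: about 4–8% at shares of 10–20%.

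**Effect on type I error (null simulations, nominal 5%).**
- Two practice-level and seven patient-level candidates, none prognostic; 49 practices of 41 patients, ICC 0.05, continuous outcome, no stratification: 5.1% after forward selection, 4.9% unadjusted (Monte Carlo SE about 0.35 points).
- Stratified allocation, the two named practice-level candidates, PCT not a candidate, stratifiers not prognostic: 4.7% and 5.3% in two separate runs.
- The same with PCT explaining 20% and practice size 10% of between-practice variance (assumed): 3.5% and 3.8%, with the reported standard error about 9% and 7% too large.
- Nine candidates all placed at practice level, none prognostic, 48 practices: 6.5%, against 5.3% with the stratifiers forced in (Monte Carlo SE about 0.4 points). This is harsher than the plan, which names only two practice-level candidates.

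**The case against.** The strongest defence has four parts.

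- **The list is illustrative.** The practice-level covariates are introduced permissively ("The former may include practice size and deprivation index"), and a condensed article need not name everything. A reader might infer that PCT can never enter the model. The text does not support that; it supports only that PCT is not named and nothing requires it. The defence does not reach the selection rule, which is stated outright and would carry over into any analysis plan that followed it.
- **The rule is an algorithm.** Given a closed candidate list, forward selection at a stated threshold returns one model, so the 512 subsets do not measure analyst freedom. That is right. The freedom lies in the open list, and the dependence on outcome data remains.
- **Error rates barely move.** A reader might conclude that the nominal interval and p-value are unsound. The simulations do not support this. The 6.5% needs nine practice-level candidates, and with the two that are named, rejection stays near 5% or falls below it.
- **The screen mostly discards what matters little.** A covariate worth 5% of between-practice variance is usually dropped but costs only 1.8% in interval width; one worth 20% is kept 86% of the time. This is fair for practice size. It gives no comfort for PCT, which need not be screened at all.

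**Conclusion.** The point stands as a should-fix. The primary model is not fixed before outcome data are seen, and it is not tied to the factors used in randomization. The main consequence is an interval that is too wide and a conservative test if PCT or practice size is prognostic and left out. For PCT this is about 4–8% in width at an assumed 10–20% share of between-practice variance. If PCT explains nothing, omitting it costs nothing. Selection itself leaves coverage not guaranteed nominal, with little inflation of type I error from the named candidates. The simulations use continuous outcomes or practice-level summaries rather than the full mixed logistic model, so they show direction and rough size only. Lack of prespecification and the shifting odds ratio depend on none of these figures.

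**What to change.** Delete the forward-selection sentence for the primary and secondary models. In its place, prespecify:

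- trial arm, PCT and the practice-size stratum as used in randomization, all forced in as fixed effects, with a practice random intercept;
- baseline HbA1c, blood pressure and cholesterol, which are the risk factors that make up the outcome and are measured at the baseline assessment;
- any further covariates taken from the list in the Statistical analysis section, chosen and recorded before outcome data are seen. Which of these to keep is for the trial team.

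Report a model with arm and stratifiers only as a sensitivity analysis. State that area and PCT are the same stratifier, if they are. The Discussion reports follow-up as finished, so date the change and record that outcome data had not been examined when it was made.

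**Cost.** Wording only; no new data are needed and no stated sample size changes. Three PCTs use 2 practice-level degrees of freedom, and practice size uses 1 if it has two strata (the number is not stated). With 49 practices that leaves 49 − 1 − 1 − 2 − 1 = 44 after intercept, arm, PCT and size.

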### Sample size

We initially planned to recruit a total of 5,000 patients from 51 practices (25 in one trial arm, and 26 in the other), with approximately 100 patients being recruited from each practice. Due to losses during follow-up, we expected the final number of patients in each practice to be 72, or approximately 3,700 patients in total.

Estimates for the percentage of patients achieving control in the usual care group are taken from a UK survey [4]. We used HbA_1c_ for our primary sample size calculation as this is the outcome variable for which there is the most robust information on intra-class correlation (ICC). To detect a difference of percentage well-controlled (HbA_1c_ <7.5%) from 50% in the control group to 60% in the intervention group (α = 0.05, Power = 0.8not allowing for clustering, requires a sample size of 408 subjects in each arm. Using an Intra-class correlation (ICC) of 0.047, and with 72 patients in each cluster, the necessary sample size in each arm is 1770, representing a total of 3,540 patients for both arms. This number is also adequate to detect a 10% difference in cholesterol control (from 60% to 70%) and blood pressure control (from 60% to 70%). Estimates of ICC for blood pressure and cholesterol are taken from the UK Asian Diabetes Study (UKADS), a study of care provision for people of South Asian ethnicity with diabetes [30]. Assuming the ICC for our combined primary outcome (adequate control of HbA1C, blood pressure and cholesterol) is 0.05 and achievement is at 20% in the control arm and 30% in the intervention arm, we would need a total of 2,848 patients.

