### Study intervention

Following development work, community-based ICCDs were established in the participating PCTs. These are designed to work closely with hospital-based specialist teams and community services, including podiatry and dietetics, in order to support primary care, particularly smaller practices that have the most difficulty achieving good control for their patients. Each ICCD consists of a multidisciplinary team, led by a specialist nurse, with emphasis placed on education and self-management. Medical care is provided by a diabetes specialist or a GP with a special interest (GPwSI) in diabetes and, in practices with access to the service, patients with T2DM are no longer referred to hospital directly. Guidelines for referral to the ICCDs are common across all sites, and include people with poorly controlled T2DM and those with poorly controlled cardiovascular risk factors. Patients are managed by the ICCD team until control of risk factors is achieved and then participants are referred back to primary care. The team members work to local guidelines, adapted from national evidence-based guidelines [32].

At both sites the planned capacity is for 20% of patients with T2DM to attend the ICCD per annum, assuming that on average patients will be seen four times in the ICCD before returning to primary care.

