### Trial procedures

#### Practice recruitment

The study team first contacted all practices in the relevant PCTs. Practices were sent an invitation letter and short information sheet via the post, and invited to express an interest in participating in the trial. For practices that express an interest, data on current levels of control of patients with T2DM were examined (% patients with HbA_1c_ <7.5, BP145/85 mmHg or less and cholesterol 5 mmol/l or less). These are routinely collected as part of the GP contract [42] and those practices with the highest proportions of poorly controlled patients were invited to join the study.

Practices are recruited on the understanding that they will have access to results on weight, blood pressure, lipids, HbA_1c_ and microalbuminuria from the assessments of patients belonging to their practice. Blood and urine samples are sent to the laboratory for analysis and results sent to practices in the usual way. Research staff record the patient’s blood pressure and weight in the patient’s electronic health records, subject to prior permission from the practice.

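### About 25 intervention practices share a few ICCD teams, but only clustering by practice is allowed for: the pooled interval holds for these ICCDs and does not by itself support a claim about ICCDs in UK primary care

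*Protocol article*

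**What the plan says.** All places are in the protocol article.

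- **Randomization.** Practices are the unit (Study design). Allocation was stratified by practice size and PCT (Practice randomization). The Discussion reports 49 practices randomized, so about 25 are in the intervention arm.
- **Delivery.** Each ICCD is one nurse-led multidisciplinary team, and ICCDs were set up in the participating PCTs (Study intervention). Background puts the number of PCTs at three. Study intervention then says "At both sites the planned capacity is for 20% of patients with T2DM to attend the ICCD per annum". No section gives the number of teams.
- **Medical input.** "Medical care is provided by a diabetes specialist or a GP with a special interest (GPwSI) in diabetes" (Study intervention).
- **Analysis.** The odds ratio is estimated "adjusting for potential confounding variables and allowing for the effect of the cluster randomization" (Statistical analysis). Baseline characteristics enter by forward selection at the 10% level. Practice size and deprivation are named as possible practice-level covariates; PCT is not named.
- **Claim.** The study "will provide a robust estimate of the effects of introduction of intermediate care clinics for diabetes" in UK primary care, and is meant to inform commissioning (Discussion).

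**The concern.** Practices in the intervention arm that use the same ICCD share its staff and way of working. If one team achieves more than another, all practices attached to it move together. That variation lies above the practice and exists only in the intervention arm. A model whose only cluster is the practice treats about 25 intervention practices as independent evidence on how well an ICCD works, although far fewer ICCDs were observed.

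For the question of whether access to these ICCDs helped, this does no harm. For the question a commissioner elsewhere would ask, which is what an ICCD set up by another team would achieve, the interval is too narrow by an unknown amount. A single pooled odds ratio would also hide a result in which one clinic worked and another did not.

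The adjustment rule adds a smaller problem. PCT was used to stratify the randomization and is the available marker of which ICCD a practice could use, but nothing in the stated rule guarantees it a place in the model. Practice size, the other stratum, appears only as a candidate for selection.

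**Working it through.** **1. Does the plan's own arithmetic contain anything above the practice?**

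Inputs are from Sample size; a two-sided test is assumed, since sidedness is not stated.

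- HbA1c, 50% against 60%: the article says "α = 0.05, Power = 0.8not allowing for clustering, requires a sample size of 408 subjects in each arm". The usual two-proportion formula with continuity correction gives 408. With 72 patients per practice and ICC 0.047, the design effect is 1 + 71 × 0.047 = 4.337, and 408 × 4.337 = 1,769.5. The article has 1,770: "Using an Intra-class correlation (ICC) of 0.047, and with 72 patients in each cluster, the necessary sample size in each arm is 1770".
- Combined outcome, 20% against 30%: "Assuming the ICC for our combined primary outcome (adequate control of HbA1C, blood pressure and cholesterol) is 0.05". The formula gives 313 per arm, the design effect is 1 + 71 × 0.05 = 4.55, and 313 × 4.55 = 1,424 per arm, or 2,848 in total, as stated.

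Both figures reproduce with a design effect for practice alone. The planning, like the analysis, has no term for the clinic.

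**2. What would variation between ICCDs add?**

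A 10-point difference detected with 80% power implies a standard error of 10 / (1.96 + 0.8416) = 3.57 points. Let τ be the SD of the true effect between ICCDs, in percentage points, and K the number of teams. The standard error for ICCDs in general is then √(3.57² + τ²/K), and the coverage of the nominal 95% interval is 2Φ(1.96 × 3.57 / SE) − 1. Neither τ nor K is in the article. K = 3 and K = 2 are inferred from the two phrases about PCTs and sites; τ is assumed.

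| Assumed τ | SE, K = 3 | SE, K = 2 | Increase over 3.57 (K = 3, K = 2) | Coverage (K = 3, K = 2) |
|---|---|---|---|---|
| 1 | 3.62 | 3.64 | 1%, 2% | 94.7%, 94.6% |
| 3 | 3.97 | 4.15 | 11%, 16% | 92%, 91% |
| 5 | 4.59 | 5.02 | 29%, 41% | 87%, 84% |

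**3. Cross-check from the revised design.**

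Take 1,022 patients per arm and 40 per practice (25.55 practices per arm), practice ICC 0.05, and rates of 20% and 30%. The variance of the difference is (0.16 + 0.21) × (0.95/1,022 + 0.05/25.55), so the practice-only SE is 3.27 points. Now let a share c of the intervention-arm variance (an assumed clinic ICC) lie between clinics, which adds about 0.21 × c/K.

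- c = 0.001: SE 3.37 (K = 3) or 3.42 (K = 2), up 3% or 5%.
- c = 0.005: SE 3.76 or 3.99, up 15% or 22%.
- c = 0.01: SE 4.20 or 4.60, up 29% or 41%.

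The base differs from 3.57 because it comes from the stated numbers and not from the power target. The pattern is the same.

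**4. Does a practice-level random effect pick this up?**

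Only in part. Differences between the observed clinics inflate the estimated practice variance, but the model divides that variance by about 25 practices instead of two or three clinics. At c = 0.005 and K = 2, the practice-only model would report an SE of about 3.30 where 3.99 is needed.

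**The case against.** The strongest reply is that nothing is wrong with the analysis. The trial compares practices with and without ICCD access, practices were randomized within PCT, and conditioning on the sites that took part is normal in multicentre trials. That stands. A reader might infer that the primary interval is invalid for the trial's own comparison; the article does not support that.

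Other stronger readings also fail:

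- *That the number of teams is known.* Two or three is only a natural inference.
- *That every intervention patient is treated by the ICCD.* Patients have access. Planned capacity is 20% of T2DM patients a year, and the comparison includes those who never attend (Primary clinical outcome measure). Non-attendance dilutes differences between teams, so τ may be small. Against this, Patient recruitment describes recruits as suitable for ICCD referral, so the dilution among participants may be less than 20% suggests.
- *That the article predicts different effects between its own teams.* The varied staffing and organization described in Background concerns other UK services. The specialist-or-GPwSI sentence does not say that sites differ, and referral guidelines are common to all sites. This makes variation possible, not expected.
- *That the interval contains nothing from between-clinic variation.* Some of it reaches the practice variance, as shown in step 4.

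It can also be said that stratum terms and site tables belong in an SAP, which is not shown, and that the covariate list is open-ended. This is fair as to detail. But the article does fix a selection rule, and under it practice size, a randomization stratum, is only a candidate. The Discussion also softens its claim by calling positive results an initial evidence base; the broader sentence remains.

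**Conclusion.** The point holds as a mismatch between the interval and the claim. The pooled odds ratio and its 95% interval answer the question for access to these ICCDs. They do not properly reflect variation between ICCD teams, and so do not by themselves support the Discussion's statement about ICCDs in UK primary care.

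The size of the shortfall cannot be obtained from the article, which gives neither the number of teams nor any between-clinic variance. On assumed SDs of 1 to 5 points and two or three teams, it ranges from negligible (1-2% on the standard error) to substantial (29-41%). The upper end is a severe assumption: an SD of 5 around a 10-point effect would mean true clinic effects from about 0 to 20 points (two SDs either side), which nothing in the article suggests.

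A random clinic effect may look like the obvious remedy, but with two or three teams there are only 1 or 2 degrees of freedom (t quantiles of 12.7 and 4.3), so the component is practically not estimable. The workable response is stratified reporting and a narrower conclusion. That participating practices were chosen because "those practices with the highest proportions of poorly controlled patients were invited to join the study" (Practice recruitment) is a separate limit on generalization, and another reason to tie the conclusion to the participating practices.

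**What to change.** 1. In Statistical analysis, include PCT and the practice-size stratum as fixed effects in the primary model, whatever forward selection does with other covariates. Keep the single pooled odds ratio as the primary result.
2. Pre-specify a separate companion model with an arm-by-PCT interaction, and report the arm effect with its 95% interval for each PCT/ICCD as descriptive. The interaction should stay out of the primary model, because under the usual reference coding the arm coefficient would then be the effect in one PCT only.
3. State the number of ICCD teams and which practices could use each, and reconcile the three PCTs with the two sites.
4. State that the pooled interval is conditional on these ICCDs, and limit the Discussion's conclusion to these ICCDs in the participating practices.

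No new data are needed: the cost is two stratum terms, one small table and a more modest claim. The site-specific intervals will be wide and the interaction test will have low power, so similar estimates would not show that the teams are equally effective. Differences between sites cannot be separated from differences between PCTs, so the table would not show which clinic model works best.
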